## Abstract

**Background:**

Sleep disturbance in older people is an important health issue that is associated with many other health problems. Effective interventions are required to address sleep problems in this group. Acupressure has been suggested as a potential therapeutic technique to improve sleep. The aim of this study is to evaluate the effects of an acupressure intervention on sleep quality, anxiety, depression, and quality of life among older persons in residential aged care facilities within an Australian context.

**Methods/design:**

This is a randomised controlled trial with two parallel groups in a pre- and post-test study. Study participants will be older people living in residential aged care facilities. They will be assigned to intervention and control groups using computer-generated random numbers. The intervention group will receive 12-min acupressure three times per week for four consecutive weeks, applied on three acupoints: HT7, PC6, and SP6. The control group will receive only routine care. The primary outcome measure is sleep quality, and secondary outcomes include anxiety, depression, and quality of life. Data will be collected before the intervention, immediately after the end of the intervention, and 2 weeks after the intervention.

**Discussion:**

This study targets a poorly met healthcare need of older people who are experiencing sleep disturbance and its negative consequences. To the researchers’ knowledge, this is the first study evaluating acupressure in an Australian aged care context, using specific acupoints and a standardised acupressure protocol. If the results show positive outcomes, acupressure could be used to manage sleep disturbances for older people in the Australian context as well as in the global ageing population. This will contribute to reducing negative consequences of sleep disturbance and use of sleep medications.

**Trial registration:**

Australian New Zealand Clinical Trials Registry: ACTRN12619000262101. Registered on 20 February 2019.

## Introduction

Sleep disturbances increase with advancing age, with the prevalent rate approaching 50% in older people aged 65 and above [1]. Sleep disturbances in older persons are associated with poor health status, cognitive decline, depression, poor quality of life (QoL) and higher risk of falls [1, 2]. Recent systematic reviews and meta-analyses found that sleep disturbances contributed to higher risk of dementia [3], mental illnesses including anxiety and depression [4], hypertension [5], and cardiovascular disease [6]. Sleep disturbances are also found to have a bidirectional relationship with depression and anxiety [7]. Insomnia and sleep problems were related to high level of anxiety and depression; on the other hand, anxiety and depression were related to insomnia [7].

These health and psychosocial issues are especially pertinent for older people in residential care. The prevalence of sleep disturbance is higher among older people in residential care than among those living in the community [8–11]. A study conducted in Spain showed that a high percentage of nursing home residents (72.1%) were poor sleepers, and poor sleep quality was found to be correlated with decline in functional status [10]. In a European study, the prevalent rate of insomnia in long-term care residents was 24% (ranging from 13% to 30%) [8]. Authors of a narrative review of sleep among long-term care residents in China reported that the prevalence of poor sleep quality ranged from 33% to 73% [9]. In Australia, 47.3% of residents in aged care had poorer night-time sleep quality [12]. The high prevalence of sleep problems in this population is a global health concern that needs to be addressed. Promoting sleep quality may have a positive impact on its associated conditions such as depression, anxiety, and poor QoL.

## Background

Sleep disturbance in the older population is a worldwide health issue that is associated with many health conditions and increased healthcare burdens [1, 13]. Sleep disturbances comprise a broad range of clinical conditions: difficulty in initiating or maintaining sleep, excessive daytime sleepiness, and disrupted sleep–wake patterns [7, 14]. Sleep disturbance in older people is a multifactorial geriatric health issue that calls for a comprehensive treatment approach, with consideration of multiple risk factors such as comorbid diseases, side effects of medications, and psychosocial factors [1, 13]. Integrating conventional medical treatment with complementary therapy to address this clinical issue might be beneficial.

Sleep disturbance in older people is often treated with medications, which have potential adverse effects: drowsiness, poor concentration, loss of memory, and drug dependence [15, 16]. These adverse effects contribute to risks of falls, accidents, and cognitive impairment with long-term use of sleep medications [13, 17]. To avoid the adverse effects of sleep medications, a non-pharmacological treatment approach has been recommended to manage sleep disturbances in older people [17, 18]. Use of complementary and alternative medicine (CAM) may be beneficial for sleep improvement in older people.

Acupressure, application of fingers or thumb pressure on acupuncture points, is a CAM modality which has potential to improve sleep quality [19–21]. Previous research and reviews have shown that acupressure improved sleep quality with no reported adverse effects [19–24]. In addition, acupressure may have potential to reduce the frequency and amount sleep medications used [23, 25]. This can further reduce the cost and side effects of sleep medications. There is also some evidence that acupressure may improve depression [19], anxiety [26] and QoL [21]. However, some studies have methodological limitations as well as variation in acupressure techniques and the selection of acupoints [19, 20, 26]. Future well-designed studies, using standardised treatment protocols, are required to provide evidence of acupressure’s usefulness in clinical practice.

Acupressure is a simple technique which can be administered by nurses with minimal training. Integrating acupressure into aged care settings may be beneficial to promote sleep quality and wellbeing, without having harmful side effects. However, the acceptability and effectiveness of acupressure on sleep improvement remains unclear in the Australia aged care context. The majority of the acupressure studies were carried out in Asian countries (in Taiwan, China, and Hong Kong), and the participants were Chinese who might have had beliefs in traditional Chinese medicine (TCM) [19, 20]. There is a paucity of studies evaluating the outcomes of acupressure in Western countries, including Australia [19, 20]. Acupressure studies conducted in Western populations would enhance the generalisability of the findings. Thus, it is timely to test the efficacy of a standardised acupressure intervention protocol, with well-defined techniques applied on specific acupoints, in residential aged care facilities (RACFs) within the Australia context.

In this study, we focus on sleep quality as the primary outcome because sleep disturbance in this age group is a significant issue which has negative impacts on health status. We will measure anxiety, depression, and QoL as secondary outcomes that are associated with sleep disturbances. The findings of this study will provide important implications and recommendations for future implementation of acupressure intervention in the Australian aged care context, as well as in the worldwide general population with sleep disturbances.

### Acupressure for sleep

Acupressure is the stimulation of acupuncture points (acupoints) on the meridian lines using finger or thumb pressure [27]. The purpose of acupressure is to regulate the vital energy (known as *Qi*) that maintains the person’s health and wellbeing [27]. Manual stimulation of acupoints helps release muscle tension, promotes blood circulation, and strengthens immunity [27, 28]. In the TCM perspective, health is considered as having the normal flow of a vital energy and balance between *Yin* and *Yang* [29]. When *Qi* flows freely, the person is healthy and well-balanced. If there is insufficient *Qi*, or normal movement of *Qi* is impaired, dysfunction occurs, and then physical, emotional, and mental illnesses develop. In the condition of sleep disturbances, it is a result of internal disharmony in *Qi* flow, *Yin* and *Yang* imbalance, and dysfunction of the internal organs [30]. Application of acupressure regulates *Qi* flow within the body or in a specific organ, restoring good health and improving sleep quality [27, 31].

### Acupoints for sleep improvement

In TCM, sleep problems are associated with dysfunction of the heart and other organs, including the spleen, liver, kidneys, and stomach [24, 30]. Therefore, selecting the major acupoint on the heart meridian (HT7) and additional acupoints that are linked to other internal organs (PC6 and SP6) may enhance sleep quality. The acupoints—namely, *Shenmen* (HT7), *Neiguan* (PC6), and *Sanyinjiao* (SP6)—have commonly been used to improve sleep quality [19, 20, 32, 33].

***Shenmen*****(HT7)** is an important acupoint along the heart meridian that passes through and ends in the heart [24]. *Shenmen* is described as the ‘spirit gate’ that is a pathway related to vitality and stabilises mental state, and it is believed to calm the nerves and ease the mind [31]. In TCM, dysfunction of the heart is thought to be a major cause of sleep disturbance. Therefore, pressure applied to the *Shenmen,* the major point of the heart channel, is thought to regulate sleep function [20, 31]. As shown in Fig. 1, HT7 is located on the palmar wrist crease at the depression radial to the proximal border of the pisiform bone [34].

**Fig. 1 Fig1:**
[figure not shown]
Location of selected acupoints

***Neiguan*****(PC6)** is the connecting point of the pericardial meridian (PC) that controls the functions of the heart and respiration [35]. This acupoint is commonly used for nausea and vomiting, but it can be used to treat illnesses related to the heart, lungs, and stomach and mental problems. The *Neiguan* regulates the heart *Qi*, opens the chest, harmonises the stomach, and calms the spirit. Acupressure on applied on *Neiguan* could relieve insomnia, dyspnoea, cough, tightness of chest, nausea, vomiting, motion sickness, headache, depression and anxiety [35, 36].

In TCM, dysfunctions of the heart and stomach could be related to sleep disturbances [30]. Thus, the *Neiguan* is a useful point that regulates normal functions of the heart and stomach, thereby relieving sleep problems and associated symptoms. PC6 is located at the anterior aspect of the forearm, between two tendons (the palmaris longus and the flexor carpi radialis), 2-*cun* proximal to the palmar wrist crease (shown in Fig. 1) [34].

***Sanyinjiao*****(SP6)** is one of the commonly used acupoints because it is located at the intersection of three *Yin* meridians: the spleen, kidney and liver meridians [35]. This acupoint can be used to treat the conditions related to urogenital disorders, menstruation, childbirth, menopause, indigestion, insomnia and emotional imbalances [35, 36].

According to TCM, sleep disturbance is also caused dysfunctions of spleen, kidney and liver; thus, stimulating the *Sanyinjiao* is commonly applied to improve sleep [24, 30]. SP6 is located on the tibial aspect of the leg, posterior to the medial border of the tibia, 3-*cun* superior to the prominence of the medial malleolus (shown in Fig. 1) [34].

TCM emphasises the individualised nature of therapy, and therefore individualised treatments are given depending on the patient’s conditions [31, 36]. However, in research and clinical practice, standardised acupressure protocols are required, with clearly defined technique and specific acupoints. In this study, finger or thumb pressure applied on three specific acupoints—HT7, PC6 and SP6—is expected to produce a positive effect on sleep quality.

### Study aim and hypotheses

This study aims to evaluate the effects of an acupressure intervention, using three specific acupoints (HT7, PC6 and SP6), on sleep quality, anxiety, depression, and QoL of older people in RACFs in Australia.

### Hypotheses

After the intervention, compared with the control group, the experimental group receiving acupressure would have:
Significant improvement of sleep quality,Significant reduction of level of depression and anxiety, andSignificant improvement of QoL.

## Methods/design

### Study design

A randomised controlled trial with two parallel groups, pre- and post-test design, is proposed. The study protocol followed the Standard Protocol Items: Recommendations for Interventional Trials (SPIRIT) checklist (Additional File 1). The study participants will be randomly assigned to the intervention group, receiving 12-min acupressure sessions and routine care, or the control group, receiving routine care only.

### Setting and participants

This study will be conducted in three RACFs (RACFs 1, 2 and 3) in New South Wales State, Australia. The selected study venues are facilities accredited by the Aged Care Quality and Safety Commission, Australia. These facilities offer general healthcare for the residents and specialised aged care services, such as dementia care and palliative care. Study participants will be older people residing in the study venues.

### Inclusion and exclusion criteria

The inclusion criteria to participate in this study are (i) aged 65 and above, (ii) a resident of an aged care facility or a retirement village, (iii) have self-reported poor sleep quality, (iv) able to communicate, and (v) able to give written consent to participate and do so. Self-reported poor sleep quality will be identified on the basis of residents’ subjective complaint of disrupted sleep, having sleep problems or poor sleep quality. When potential participants express interest in the study, the researcher will ask them whether they have sleep problems or disturbed sleep.

The exclusion criteria are (i) severe cognitive impairment that would limit the accuracy of assessment; (ii) amputation or recent fracture of upper or lower limbs, because the selected acupoints are located on both hands and legs; (iii) severe illness, presence of blood clotting disorders such as thrombophlebitis, or bleeding disorder such as haemophilia to avoid potential complications; (iv) currently taking blood thinning medication, anti-coagulants and anti-clotting agents; and (vi) presence of skin lesions, infection or inflammation near selected acupoints. Cognitive function level will be determined on the basis of the Mini Mental State Examination (MMSE) record used in the facility. An MMSE score of 9 or lower is considered as severe cognitive impairment in older populations [37].

### Sample size estimation

The sample size estimation is based on a previous study that indicated statistical significance in sleep quality between intervention and control group [23]. The mean difference of sleep quality (Pittsburgh Sleep Quality Index [PSQI] score) between groups was 5, and the pooled standard deviation was 6.35. To detect a mean difference of 5 points (assuming a standard deviation of 6.35), 26 participants in each group are required for a power of 0.80 and *P =* 0.05. Considering a 10% attrition rate, 29 participants in each group, with a total of 58 participants, are required.

### Randomisation

Block randomisation with 1:1 allocation ratio will be used. Block sizes of 4 and 6 will be used. The random sequence numbers will be produced by using an internet tool (www.sealedenvelope.com). Sealed envelopes with sequential numbering will be used to conceal group allocation. Blinding is not possible in this study, because it has limited funding to employ assistants for data collection and acupressure intervention. Therefore, the primary researcher will perform the acupressure and will collect and analyse the data.

### Acupressure intervention and routine care

The participants assigned in the intervention group will receive acupressure and routine care offered in the selected RACFs. The control group will receive routine care only. During the intervention period, participants in both groups will be allowed to take prescribed medications and go for their routine daily activities. The research team does not control any routine activity and prescribed treatment, including sleep medication.

#### Acupressure intervention

The acupressure intervention runs for 4 weeks, with 12-min session to be given three times per week. The acupressure intervention protocol has been developed on the basis of TCM concepts, research evidence [22, 23, 38, 39], and systematic and integrative reviews on acupressure studies [19, 20, 32]. One of the supervisors is a qualified acupressure practitioner. She has supervised the design of the acupressure intervention protocol.

The intervention ‘dosage’ is based on the findings of systematic and integrative reviews [19, 20, 32]. Systematic reviews suggested that acupressure was most effective when applied three or more times per week for a minimum of 3 weeks [20], and a 4-week duration was most commonly used [32]. Finger pressure applied on each acupoint should be a minimum of 1 min [20], and 2–3 min duration applied on each point [19, 32]. In this study, pressure will be applied for 2 min on each acupoint—HT7, PC6 and SP6—on both hands and legs, thus a total of six points for both sides with 12-min duration. Table 1 shows the acupressure intervention protocol.

**Table 1 Tab1:** Acupressure intervention protocol

Acupressure sessions and length of intervention	• 12-min session, three times per week for 4 weeks • Daytime (9 a.m.–5 p.m.), following the convenient time for study participants
Selection of acupoints	1. Shenmen (HT7) on both hands 2. Neiguan (PC6) on both hands 3. Sanyinjiao (SP6) on both legs
Sequence and time of acupressure application per point	Apply finger pressure for 2 min on each point with the following sequence: 1. PC6 in left hand 2. PC6 in right hand 3. HT7 in left hand 4. HT7 in right hand 5. SP6 on left leg 6. SP6 on right leg
Acupressure technique	• Apply consistent finger or thumb pressure on each point in circular motion • Circular motion in clockwise for 1 min and counter-clockwise for 1 min • Intensity of pressure adjusted according to the person’s level of tolerance

The student researcher (first author) will perform the acupressure intervention. She has experience in general nursing practice and nursing education. She has received training in acupressure technique from a qualified Chinese medicine physician and has performed similar acupressure intervention in her previous postgraduate research. To enhance her skills in acupressure for the present study, she attended acupressure practitioner training in Australia. During the training period, she had practised accuracy of acupoint location and acupressure technique with healthy persons, under supervision of the acupressure trainer, who has extensive experience in acupressure practice and training. Before conducting the acupressure intervention sessions, she rehearsed the acupoint locations and acupressure technique with healthy volunteers, which is verified by the co-researcher, who is expert in acupressure.

To ensure intervention fidelity, the student researcher will perform acupressure following the intervention protocol (Table 1). She will keep field notes that record the date and time of each acupressure session, as well as the observation of participants’ general condition during each acupressure session. To minimise potential discomfort of participants during the treatment, the student researcher will assess the participant’s response, and the intensity of pressure will be adjusted according to the person’s level of tolerance. She will also observe any issue or adverse event that occurs during the intervention period. If any untoward effect occurs, the student researcher will stop doing acupressure on the affected person and report to the nurse in charge and the facility manager. The student researcher and supervisors will have regular meetings to discuss the progress of the study, as well as any issues and concerns related to the study.

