### Data collection

Data collection will be carried out by the researcher for pre-test, post-test, and 2-week post-test. The data collection timeline is shown in Table 2. The baseline data collection (pre-test, T0) will be conducted before commencing the acupressure intervention, using a structured questionnaire for demographic and clinical data and validated assessment tools for sleep quality, depression, anxiety and QoL. Demographic and clinical data include age, sex, marital status, number of children, education level, residential status, length of stay in facility, source of funding, presence of chronic disease, and medications.

**Table 2 Tab2:** Data collection timeline

Stages	Enrolment	Pre-test T0	4-Week acupressure intervention				Post-test, T1		Follow-up, T2
Time point	Week 0	Week 1	Week 2	Week 3	Week 4	Week 5	Week 6	Week 7	Week 8
Recruitment and consent	4–6 weeks								
Baseline assessment: - Demographic and clinical data - ActiGraph - PSQI, HADS, OPQOL-Brief		X							
Intervention: IG: acupressure + routine care CG: routine care			X	X	X	X			
Post-test outcome assessment: - ActiGraph - PSQI, HADS, OPQOL-Brief							X		
Follow-up assessment: - ActiGraph - PSQI, HADS, OPQOL-Brief									X

*CG* Control group, *HADS* Hospital Anxiety and Depression Scale, *IG* Intervention group, *OPQOL-Brief* Older People’s Quality of Life questionnaire–brief version, *PSQI* Pittsburgh Sleep Quality Index

The outcome assessments will be conducted at the end of intervention (post-test, T1) and 2 weeks post-intervention (post-test, T2). The participants will receive only routine care after the intervention period. The purpose of the follow-up test (T2) is to assess whether the treatment effect of acupressure can be retained 2 weeks after the intervention. For the control group, baseline and outcome data (T0, T1 and T2) will be collected using the same set of questionnaires and following the same time frame as in the intervention group. The student researcher will provide the assessment tools to the participants and assist them in completing the questionnaires if needed.

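### Adverse-event ascertainment is unblinded, framed around treated residents and ends before T2, so harms cannot be compared between arms (minor)

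*Protocol article*

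**What the plan says.** Harms collection appears only in the Acupressure intervention section of the protocol article. The student researcher who gives the treatment keeps field notes on session dates and times and on "the observation of participants’ general condition during each acupressure session". The article then adds: "She will also observe any issue or adverse event that occurs during the intervention period". The response to an event is also given: "If any untoward effect occurs, the student researcher will stop doing acupressure on the affected person and report to the nurse in charge"; the facility manager is informed as well.

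The Routine care section has no harms text. Under Data collection, the control arm is covered by this: "For the control group, baseline and outcome data (T0, T1 and T2) will be collected using the same set of questionnaires". Table 2 lists demographic and clinical data at baseline, and ActiGraph, PSQI, HADS and OPQOL-Brief at T0, T1 and T2. It has no adverse-event row for either arm. One purpose is given for the last visit: "The purpose of the follow-up test (T2) is to assess whether the treatment effect of acupressure can be retained 2 weeks after the intervention".

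The Randomisation section says that blinding is not possible and that "the primary researcher will perform the acupressure and will collect and analyse the data".

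**The concern.** A harms count can be interpreted only if events are looked for in the same way, over the same time, in both arms. Here the observer is the therapist, the surrounding text concerns people receiving acupressure, and the stated window closes when treatment ends.

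The Discussion describes residents with chronic conditions and several prescribed medicines, so some events will occur in either arm whatever the treatment. If they are noted mainly in the acupressure arm, background illness can look like harm from acupressure. If the therapist does not notice them, or they appear after the last session, the silence can look like safety. The protocol itself expects that physical complications are possible: it excludes residents with clotting or bleeding disorders for that reason. The Limitations section acknowledges the missing blinding and sham control but not the one-sided collection of harms.

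**Working it through.** **1. The text by arm and period** (Table 2 puts the intervention in Weeks 2 to 5, T1 in Week 6 and T2 in Week 8)

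| | Acupressure arm | Control arm |
|---|---|---|
| Intervention period | Therapist's session notes; therapist observes events; stop-and-report action | No harms enquiry described |
| T1 | Sleep, mood and QoL measures only | The same measures only |
| T2 | The same measures; purpose is retention of effect | The same measures only |

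The observation sentence names no arm. Three things tie it to treated residents: it sits in the acupressure section, it follows the session notes, and the action after it (stopping acupressure) cannot apply to a control.

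**2. What unequal ascertainment does to a comparison**

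Let the true event risks be p1 (acupressure) and p0 (control), and let the proportions of events captured be c1 and c0. The expected observed risks are p1 × c1 and p0 × c0, so

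observed risk ratio = (p1/p0) × (c1/c0).

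The observed ratio equals the true one only if c1 = c0. Nothing in the article makes the two equal. If no control events are captured, c0 = 0 and the ratio does not exist. The documents give neither c1 nor c0, so I put no number on the bias.

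**3. The plan's sample size, as the denominator for harms**

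Inputs from Sample size estimation: difference 5, SD 6.35, power 0.80, P = 0.05 (two-sided assumed, as sidedness is not stated), attrition 10%.

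- n per arm = 2 × (1.960 + 0.842)² × 6.35² / 5² = 2 × 7.85 × 40.32 / 25 = 25.3, rounded up to 26.
- 26 / 0.90 = 28.9, rounded up to 29 per arm, 58 in total.

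Both stated figures reproduce.

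**4. What zero events could show, even with complete capture**

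The one-sided 95% upper limit solves (1 − p)^n = 0.05, so p = 1 − 0.05^(1/n). For the two-sided 95% interval, 0.025 replaces 0.05.

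| n treated | One-sided 95% limit | Two-sided 95% limit |
|---|---|---|
| 29 | 9.8% | 11.9% |
| 26 | 10.9% | 13.2% |

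The chance of at least one event among 29 is 1 − (1 − p)^29. For assumed true risks of 1%, 2%, 5% and 10% it is 25%, 44%, 77% and 95%.

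These figures depend only on n. They would be the same after the fix, so they show how cautious a safety statement must be and do not measure the collection defect.

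**The case against.** The strongest reply is that this is a condensed article. The Trial status section refers to protocol versions 3 to 5, which are not shown and may contain symmetric harms procedures. That stands as a caveat. However, the article does more than stay silent: it states an observer and a window, and it sets out the assessment schedule. What it states is one-sided.

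It can also be said that the observation sentence is not restricted to one arm, and that the article elsewhere uses the same period for both groups. That is fair as to wording, so control coverage is best called undescribed rather than excluded. The end of the window before T2 does not depend on this reading.

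A reader might go further in three ways that the documents do not support:

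- **That the trial fails its own premise of safety.** The Background says "Integrating acupressure into aged care settings may be beneficial to promote sleep quality and wellbeing, without having harmful side effects". This is hedged rationale that rests on earlier literature. Safety is not among the aims, hypotheses, outcomes or analyses. Sample size alone would in any case rule out a no-harm conclusion.
- **That harms are seen only during the session minutes.** The stated window is the whole intervention period, and a therapist visiting three times a week can hear of events between sessions. Session time is not a capture rate.
- **That falls are a named risk of acupressure.** The Introduction and Background link falls to sleep disturbance and to sleep medication, not to acupressure.

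Two further objections hold. The single unblinded researcher is already disclosed. And the article describes record use only for eligibility and cognitive status, so extracting events from facility records may need consent or ethics cover that cannot be seen here.

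**Conclusion.** The point holds as a minor design weakness. As described, adverse-event ascertainment is unblinded, framed around treated residents and finished before T2, so the trial cannot support a between-arm comparison of harms. The conclusion assumes that the article reflects the full procedure; a symmetric enquiry in the full protocol would remove it.

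The size of any ascertainment bias is unknown. The 9.8% limit for zero events in 29 is a separate constraint on what may be said about safety. No efficacy estimate, test or sample-size figure is affected.

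**What to change.** - Ask every participant in both arms the same short, open harms question at T1 and T2, so that together the answers cover T0 to T2.
- Report counts by arm descriptively. List events observed at sessions separately, because sessions exist in one arm only.
- Make no statement that harm is absent without an exact upper confidence limit beside it.
- Add extraction from facility records only if consent and ethics approval cover it, and then identically in both arms.
- If the full protocol already collects harms symmetrically through T2, state that in one sentence.

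The cost is a few minutes at visits that already take place, with no extra staff or visits, and a more cautious safety statement. The same unblinded researcher would still ask the question, so the change makes timing and method equal but does not remove observer bias.

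The Trial status section says the project was completed in April 2020. If the question was not asked then, what remains is to describe the collection as it was done, report harms descriptively with the upper limit, and carry the symmetric enquiry into the larger study foreseen under Limitations.
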